### Plans to give access to the full protocol, participant level-data and statistical code {31c}

The full trial protocol will be shared on reasonable request. Anonymised data on group level may be shared with scientists who have medically or scientifically well-founded reasons; data protection according to GDPR and ethics according to ethical approval must be ensured.

## Oversight and monitoring

### Composition of the coordinating Centre and trial steering committee {5d}

#### Trial steering

Trial design and study protocol, critical review trial-related documents, supervision of trial organisation and conduct of trial.

#### Data manager

Design of and support of randomisation and eCRF system, study drug distribution.

#### Coordinating investigator

Design, study protocol and revisions, application/amendments to medical drug agency and ethics, trial registration, preparation of trial-related documents, organisation of national trial meetings, newsletter, annual safety reports, review severe adverse event (SAE) reports.

#### Principle investigators ancillary studies

Study design, protocol, related trial documents and conduct of studies.

#### Principle investigators and study nurses at study sites

Principal investigator takes responsibility for supervision of the trial at each study centre and ensures compliance with study protocol.

Assigned study nurses ensure follow-up according to protocol and delegations

### Composition of the data monitoring committee, its role and reporting structure {21a}

A data safety committee regularly reviews SAE reports and decides upon discontinuation of the trial in the event of severe delay of recruitment or severe quality deficiencies.

The trial is monitored by an experienced and independent monitor. First monitoring is performed after the first inclusions, and thereafter at least once per year. Study sites with high inclusion rates are monitored at least twice per year.

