### Interim analyses {21b}

No interim analysis will be performed.

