### Adverse event reporting and harms {22}

In this study, an adverse event is defined as any untoward medical occurrence in a participant without regard to the possibility of a causal relationship.

Expected events such as symptoms from disease or known side effects form oncological or surgical treatment or from the study drug are *not* regarded as AE. Examples for expected events are progression of malignancy, including fatal outcome, laboratory deterioration, hospitalisation due to malignancy progress/symptoms as they are expected due to the nature of a progressing disease and planned hospital visits such as for chemotherapy treatment. Other possible expected events are local reactions and overreactions at injection site (not regarded as AE but documented in the eCRF), increased body temperature ≤ 38C, and treatment failure of the study drug.

Unexpected events are to be reported as AE. In case of any doubt, investigators are instructed to report.

If an adverse event is considered serious, severity and possible relationship to study drug are defined and the SAE is reported by fax to the coordinating investigator at the sponsor site via a SAE form; a final report is sent when the SAE is resolved. Suspected Unexpected Serious Adverse Reactions (SUSARs) are reported by the coordinating investigator (or designee) to the Swedish Medical Product Agency within 24 h of knowledge or at the latest on the following working day.

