Many cancer patients use and value complementary therapies [64] including ME preparations [12, 14, 65] and express a wish for evidence and professional guidance in their decisions—a precondition for patient safety and satisfaction. Systematic research is needed to enable professional guidance.

The sample size of this trial was pragmatically chosen and based on previous observed effects of ME [35, 36] as well as practical circumstances and available funding. Given the short survival in this type of cohort and therefore short time until mature data are obtained, and the reasonably rapid inclusion of new patients, an interim analysis was not considered suitable.

Previous randomised trials on ME in Germany, a country with high popularity and high use of ME in general health care, have shown slower recruitment of patients with advanced stages of cancer and frequent prior ME treatment [66], as well as difficulties of enrolment and randomisation exceeding trials in conventional oncology. This is likely to be partially caused by the widespread knowledge, use and popularity of ME in Germany [67]. Sweden is a country with low usage and rare prescription of ME [65] and should therefore provide a more feasible study environment for recruitment and retainment of participants in a placebo-controlled ME trial design.

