## Trial status

The current protocol version is 3.3 (date 15 July 2020). This trial opened for recruitment on 1st June 2016 and is expected to complete recruitment by 2021.

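### Harm is not among the stated grounds on which the safety committee decides to discontinue, and the protocol describes no comparison of deaths by arm while patients are being recruited

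*Protocol article*

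**What the plan says.** In the protocol article, the section on the data monitoring committee (item 21a) fixes what the committee sees and what it decides. On the first: "A data safety committee regularly reviews SAE reports". On the second, it "decides upon discontinuation of the trial in the event of severe delay of recruitment or severe quality deficiencies". No other input and no other ground is named.

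The section on adverse event reporting (item 22) narrows what can become an SAE report. Symptoms of the disease and "known side effects form oncological or surgical treatment or from the study drug are *not* regarded as AE". The listed examples of expected events include "progression of malignancy, including fatal outcome, laboratory deterioration, hospitalisation due to malignancy progress/symptoms as they are expected".

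Four other places bear on the point:
- Interim analyses (21b): "No interim analysis will be performed". The Discussion gives as reasons the short survival and "the reasonably rapid inclusion of new patients, an interim analysis was not considered suitable".
- Who will be blinded (17a): study personnel, care providers and participants, with the data manager as the one exception, until the trial ends.
- Primary outcome (18a): survival status is looked up in the national register once all 290 participants have completed treatment.
- Trial status: "This trial opened for recruitment on 1st June 2016 and is expected to complete recruitment by 2021".

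**The concern.** The primary endpoint is death from any cause, and in this disease most deaths will be put down to progression. An extract that shortened survival would look, patient by patient, like ordinary progression to a blinded investigator. It would show only as an imbalance between the arms. The stated remit omits harm as a reason to stop, and the stated data flow leaves out the deaths that would reveal it. The written reason for having no interim analysis speaks of short survival and quick inclusion; it does not address monitoring for harm. Over a recruitment period of this length, patients could go on being randomised while evidence of harm built up that nobody was assigned to look at.

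**Working it through.** **1. The plan's own figure.** The sample size section states 90% power, two-sided 5%, hazard ratio 0.67, 290 patients.
- Schoenfeld: d = 4(1.960 + 1.282)² / (ln 0.67)² = 42.03 / 0.1604, so 263 deaths.
- Freedman: d = (1.67 / 0.33)² × (1.960 + 1.282)², so 270 deaths.

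These are 91% and 93% of 290, so the 90% is reproduced if about that share of patients die. The present point does not depend on it.

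**2. Time without a described comparison.** From 1 June 2016 to the start or end of 2021 is 55 or 67 months of recruitment. Adding 9 months of treatment for the last patient puts the survival check at about 64 to 76 months.

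**3. Route by which a death could be seen by arm.**
- SAE reports reach the committee, but fatal progression is classed as not an adverse event.
- The data manager is unblinded, but the listed duties are the randomisation and eCRF systems and drug distribution.
- The register is updated daily, but the planned check comes after everyone has finished treatment.
- No interim analysis is performed.

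Taken together, these sections describe no by-arm look at deaths before the end.

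**4. Deaths accruing meanwhile.** Assumptions: both arms alike, exponential survival with hazard h = ln 2 / median, and 290 patients accrued uniformly over T months. The medians span the article's figures, from 2.7 months (control arm of the earlier open-label trial) to 11 months (upper end for combination chemotherapy). Deaths by time t, for t up to T:

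D(t) = (290 / T) × [t − (1 − e^(−ht)) / h]

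- Mid-recruitment, lowest: T = 55, median 11, h = 0.0630, t = 27.5. D = 5.273 × (27.5 − 13.06) = 76.
- Mid-recruitment, highest: T = 67, median 2.7, h = 0.2567, t = 33.5. D = 4.328 × (33.5 − 3.89) = 128.
- Last enrolment, lowest: T = 55, median 11. D = 5.273 × (55 − 15.37) = 209, or 72% of 290.
- Last enrolment, highest: T = 67, median 2.7. D = 4.328 × (67 − 3.90) = 273, or 94% of 290.

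**5. Sensitivity to accrual.** The study setting section says that sites were added over time. If the accrual rate instead rose linearly from zero, then D(t) = (580 / T²) × [t²/2 − t/h + (1 − e^(−ht)) / h²]. Over the same T and medians this gives about 29 to 58 deaths at the calendar midpoint. It gives 71 to 123 when half the patients are enrolled (t = T × √0.5) and 169 to 258 at last enrolment.

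**6. What one harm look could show.** With d deaths and 1:1 allocation, z has mean √(d/4) × ln HR and variance about 1, so P(z > 1.96) = Φ(mean − 1.96). The hazard ratios are assumptions.

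| Deaths | HR 1.33: mean z, probability | HR 1.5: mean z, probability |
|---|---|---|
| 100 | 1.43, 0.30 | 2.03, 0.53 |
| 140 | 1.69, 0.39 | 2.40, 0.67 |

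**7. Cost in false alarms.** If the true hazard ratio is 0.67, the mean z at 140 deaths is 5.916 × (−0.400) = −2.37. The chance of exceeding +1.96 is then P(Z > 4.33), below 0.0001. If there is no effect, it is 0.025 for a single look and more over repeated looks.

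**The case against.** A reader might infer that the committee may stop only for administrative reasons. The text does not say so: it names two grounds, does not call them exclusive and does not forbid stopping for harm. Regular review of SAE reports would make little sense if the committee could never act on them.

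A reader might also infer that nobody has any means of protecting participants. That goes too far. SAEs go to the coordinating investigator, suspected unexpected serious reactions go to the medicines agency within 24 hours or by the next working day, annual safety reports are prepared, and investigators are told to report when in doubt. None of these routes, however, is described as a by-arm comparison of deaths.

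The article is a condensed account. A charter or the full protocol may say more, and the blinding section does not list the committee among those blinded. So the absence of a by-arm comparison is read from several sections together; no sentence states it. What stands is that the article sets out a specific remit with named grounds and leaves harm out. If another document grants that mandate, this section misdescribes it and still needs correcting.

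Having no interim analysis for efficacy is a reasoned choice and is not challenged here. The article describes the product as safe and well tolerated, and the earlier trial it cites found a hazard ratio of 0.49 in its favour. That lowers the expectation of harm, but the primary test is two-sided and so allows for an effect in either direction.

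Finally, a mid-trial table would not reliably expose harm. At a hazard ratio of 1.33 a single look would more often miss it than find it, and with gradual site opening fewer deaths would be available at the calendar midpoint.

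**Conclusion.** The point holds in limited form. Participant harm is not among the named grounds for discontinuation, and the reporting rules, blinding, timing of the survival check and lack of interim analysis together describe no comparison of deaths by arm during 55 to 67 months of recruitment. By last enrolment 72 to 94% of participants would already have died under uniform accrual. One look at 100 to 140 deaths would have a 0.53 to 0.67 chance of flagging a hazard ratio of 1.5. These sizes rest on assumed exponential survival, accrual pattern and harmful hazard ratios. They show that useful information would exist before enrolment ends; they are not evidence that the extract is harmful. This should be corrected, but it does not affect the validity of the primary test.

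**What to change.** State in the committee section (21a) that participant safety is a ground on which the committee can recommend discontinuation. State also that, at its regular reviews, the unblinded data manager supplies all-cause deaths and serious events, including those classed as expected, by coded arm. Describe these as harm-only reviews with no stopping for efficacy. Such reviews can only remove chances to declare benefit, so they do not inflate the false-positive rate for benefit. How the committee weighs repeated looks for harm belongs in its charter. The sections on interim analyses (21b), adverse events (22), primary outcome (18a) and the Discussion should be reconciled with this.

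The cost is a wording change, a periodic table and interim look-ups in a death register that the trial already plans to use. The table would be an added task for the data manager, whose listed duties do not now include it. No extra patients are needed.

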### Adverse event reporting and harms {22}

In this study, an adverse event is defined as any untoward medical occurrence in a participant without regard to the possibility of a causal relationship.

Expected events such as symptoms from disease or known side effects form oncological or surgical treatment or from the study drug are *not* regarded as AE. Examples for expected events are progression of malignancy, including fatal outcome, laboratory deterioration, hospitalisation due to malignancy progress/symptoms as they are expected due to the nature of a progressing disease and planned hospital visits such as for chemotherapy treatment. Other possible expected events are local reactions and overreactions at injection site (not regarded as AE but documented in the eCRF), increased body temperature ≤ 38C, and treatment failure of the study drug.

Unexpected events are to be reported as AE. In case of any doubt, investigators are instructed to report.

If an adverse event is considered serious, severity and possible relationship to study drug are defined and the SAE is reported by fax to the coordinating investigator at the sponsor site via a SAE form; a final report is sent when the SAE is resolved. Suspected Unexpected Serious Adverse Reactions (SUSARs) are reported by the coordinating investigator (or designee) to the Swedish Medical Product Agency within 24 h of knowledge or at the latest on the following working day.

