Clinical effectiveness of ME in cancer has been investigated in many studies with various designs and methodological quality—among these, more than 40 prospective randomised controlled trials [23, 31–39]. With regard to study quality and consistency of results, the best evidence exists for improvement of HRQoL and enhanced tolerability of cytoreductive therapies [32, 33, 35]. Regarding survival, a randomised controlled Serbian trial including 220 patients with advanced pancreatic cancer not eligible for palliative chemotherapy reported a median survival of 4.8 months among ME-treated patients compared with 2.7 months in the control group (HR = 0.49; 95% CI = 0.36–0.65; *p* < 0.0001). The survival benefit of ME was larger among patients with good prognostic features (6.6 vs. 3.2 months) than with poor prognostic features (3.4 months vs. 2.0 months) [36]. In addition, patients reported substantially better HRQoL and tended to gain weight when treated with ME compared to the control group [35]. Two phase I/II trials and some retrospective studies also reported favourable outcomes regarding safety and efficacy of ME in patients with pancreatic cancer [40–42]. Tumour remission under ME is rare but has been reported in some small studies and case reports, mostly applying high-dose ME directly at the tumour site [31, 43–46]. Ongoing trials investigate ME in bladder cancer (NCT02106572) and other advanced solid tumours (NCT03051477). ME are considered safe and well tolerated even among immunosuppressed patients. However, in rare cases, a generalised allergic reaction may occur [23, 24, 47, 48]. Unwanted and/or clinically significant interactions with ME and established chemotherapeutic drugs have not been observed [23, 40, 49–52].

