#### Reduction of dose

The dose is reduced if a local *over*reaction (defined as local reaction with redness > 5 cm and/or remaining for > 48 h) or malaise or flu-like symptoms according to the Common Terminology Criteria for Adverse Events (CTCAE) [53] grade ≥ 2 or fever > 38 °C (not caused by infection or tumour) with clear time correlation to dose increase and treatment days are observed. Half (=0.5 ml) of the ampoule content of the symptom-causing dose will then be used for 2 weeks, and subsequently the former symptom-causing dose, followed by the planned dose increase are given. If the symptoms recur, participants stay at the lower dose. If fever occurs due to the trial intervention, antipyretics are dissuaded, except for analgesic purposes. If an activation of local chronic inflammatory processes is observed (a very rare side-effect of ME), dosage is decreased and adapted individually.

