#### Termination of trial intervention

Study treatment is terminated after 9 months from the baseline visit. Treatment may be terminated earlier due to the participant’s own decision to withdraw consent or in case of medical, psychiatric, cognitive or other conditions occurring that may endanger the patient’s ability to comply with study protocol or complete the trial. Other reasons for early treatment termination are serious adverse events with suspected causal relationship to the study drug (such as allergic reaction CTCAE Grade ≥ 2, anaphylaxis, erythema multiforme or other events which may cause severe or permanent harm), or major violation of study protocol. The treatment might also be stopped in the very late palliative stage, if a potentially life-extending effect is no longer considered desirable.

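### Known study-drug side effects are excluded from adverse events even when serious, which conflicts with the stopping rule that calls drug-related allergic reactions serious adverse events

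*Protocol article*

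**What the plan says.** Section {22} of the protocol article opens with a broad definition: an adverse event is "any untoward medical occurrence in a participant without regard to the possibility of a causal relationship". It then removes a class of expected events and states that "known side effects form oncological or surgical treatment or from the study drug are *not* regarded as AE". Only unexpected events are to be reported as AEs. The serious route follows from the AE route: "If an adverse event is considered serious, severity and possible relationship to study drug are defined and the SAE is reported by fax". The section adds a safeguard: "In case of any doubt, investigators are instructed to report". Its examples of expected study-drug events are local reactions and overreactions (recorded separately in the eCRF), "increased body temperature ≤ 38C", and failure of the treatment.

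Three other places bear on this:

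- Termination of trial intervention, under {11b}, lists as reasons to stop treatment early "serious adverse events with suspected causal relationship to the study drug (such as allergic reaction CTCAE Grade ≥ 2, anaphylaxis", and goes on to erythema multiforme and other events that may cause severe or permanent harm.
- Background and rationale {6a} says of ME that "in rare cases, a generalised allergic reaction may occur".
- Reduction of dose, under {11b}, calls activation of local chronic inflammatory processes "a very rare side-effect of ME".

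**The concern.** The exclusion covers the study drug's known side effects as a class, at any grade and whether serious or not. Because the SAE form starts from an AE, an event shut out at the first step never reaches the second. A reaction that one section treats as an SAE is, under another section of the same document, not an AE at all.

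Two things are at stake. First, adverse events are a secondary objective and endpoint compared between arms (Objectives {7}, Outcomes {12}, Statistical methods {20a}). True reactions to ME can occur only in the ME arm, so leaving them out would make that arm look safer than it is. Second, SAE reports are the only safety input named for the data safety committee in {21a}, and the coordinating investigator also reviews them. A serious known reaction that is not classed as an SAE need not reach either.

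**Working it through.** No arithmetic applies: the protocol states no figure on this point and gives no rate for any of these reactions. The check is to apply the rules of {22} in order and compare the result with the other sections.

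1. **Definition.** An AE is any untoward occurrence, whatever its cause.
2. **Exclusion.** If the event is a known side effect of the study drug, it is not an AE. Grade and seriousness play no part.
3. **AE reporting.** What remains, the unexpected events, is reported as AEs.
4. **SAE reporting.** An AE that is considered serious goes on the SAE form.
5. **SUSAR reporting.** Among serious suspected reactions, the unexpected ones go to the regulator.

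Step 2 reverses part of step 1, because the definition disregards cause and the exclusion depends on it. Steps 2 and 4 together mean that a serious known drug reaction has no literal route to an SAE form. Expectedness is applied twice, at steps 2 and 5, although only step 5 needs it.

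Applied to the reactions that the protocol names:

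| Reaction | Called a known ME effect? | Under {22}, read literally | Elsewhere |
|---|---|---|---|
| Generalised allergic reaction grade 2 or higher, including anaphylaxis | Yes, {6a} | Not an AE, so not an SAE | SAE under Termination of trial intervention: **conflict** |
| Activation of chronic inflammation | Yes, Reduction of dose | Not an AE unless the site is in doubt | Dose lowered individually: **excluded, no contrary rule** |
| Erythema multiforme | Not stated | Reportable if regarded as unexpected | SAE under Termination: no conflict shown |
| Malaise or flu-like symptoms grade 2 or higher | Not stated | Depends on whether the site regards them as known | Dose-reduction trigger: no conflict shown |
| Drug-related fever above 38 °C | Not stated | Above the limit given for the expected temperature event, so it appears reportable | Dose-reduction trigger: no conflict shown |
| Local reactions and overreactions | Yes, {22} | Not AEs, but recorded in the eCRF | Consistent |

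The first row treats anaphylaxis as the severe form of the generalised allergic reaction named in {6a}. The conflict is therefore established for allergic reactions. The exclusion also reaches activation of chronic inflammation, and the text does not establish more than that.

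**The case against.** The strongest reply is that a coherent reading exists. The study-drug examples in {22} are mild or not safety events at all, and allergic reaction is not among them. The termination rule names allergic reaction and anaphylaxis, and a specific clause is normally taken to govern a general one. An investigator who has just stopped treatment for something that the protocol calls an SAE would have reason for doubt, and the instruction is then to report. Section {18a} also collects side effects and treatment changes at each visit, so the information is not simply lost.

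This stands to the extent that under-reporting is possible rather than certain. It does not remove the conflict. The listed events are only examples, and the governing clause covers known drug effects in general. The doubt instruction helps only a site that is in doubt, and for an effect that the protocol itself calls a side effect of ME the literal rule leaves little. Recording a side effect at a visit is neither classing it as an AE nor filing an SAE form.

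It is also fair to say that asking for a causal judgement under blinding is routine and no defect in itself. The difficulty is that here the judgement decides whether the event is counted at all.

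The article condenses a longer protocol, which may hold a list of expected events or further seriousness criteria. That lowers confidence that sites face an unresolved rule, but the conflict is in the printed text and is not a detail left out.

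A reader might infer that every systemic reaction named in the protocol is lost. The documents do not support this: erythema multiforme and malaise or flu-like symptoms are nowhere called known ME side effects, and fever above 38 °C lies beyond the stated limit. A reader might also want an expected number of missed events among the 145 ME patients. Only rarity is stated, and patients with known hypersensitivity are excluded, so any figure would rest on an invented rate.

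**Conclusion.** The point holds for allergic reaction of grade 2 or higher and anaphylaxis, where {22} and the termination rule contradict each other. It also holds for activation of chronic inflammation, which {22} excludes unless a site invokes doubt. It rests on reading the exclusion as written and on {6a} as evidence that generalised allergic reaction is a known effect.

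The likely consequence is a few single cases handled differently across the nine sites. If serious, such a case may not reach the safety committee. The AE comparison may under-count ME effects where sites follow {22} literally, and not where they follow the termination rule. A large bias between arms is not shown. AEs are among the other secondary endpoints rather than the key ones, the survival analysis is untouched, and treatment is stopped for these reactions under either reading. The change is still worth making, because it concerns serious reactions and the remedy is small.

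**What to change.** In section {22}:

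- Strike the study drug from the exclusion clause, so that suspected systemic reactions to it are AEs. Keep local reactions and overreactions in their separate eCRF item.
- State that any event that meets the seriousness criteria and has a suspected relation to the study drug, including those named under Termination of trial intervention, is always reported as an SAE.
- Use expectedness only to decide which serious reactions are SUSARs.

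Before unblinding, have the side effects already collected at visits under {18a} classified by people blind to allocation, and use the result in the AE comparison.

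The cost is a wording change, a note to the sites and one blinded review, with no new visits or patients. The wording change may count as a major modification, which under {25} needs a formal amendment approved by the ethics authority and the medicines agency. Recruitment opened in June 2016 and was expected to finish by 2021, so the new wording would act on the later patients only. For earlier patients the blinded review can repair the comparison, but it cannot restore timely committee review of an SAE that was never filed.
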